## Secondary objectives

The secondary objective is comprised of one hypothesis: that participants in treatment groups 1 and 2 will rate the program as acceptable.

# STUDY DURATION

## Design

CONSORT compliant Randomised Controlled Trial

## Study groups

Three study groups. 1) Clinician assisted computerized CBT (CaCCBT), 2) computerized CBT with reminder calls from administrative staff (CCBT), 3) waitlist control.

## Number of participants

150 in total: CaCCBT: n=50; CCBT: n = 50; Waitlist: n= 50

## Number of centres

1 – Clinical Research Unit for Anxiety and Depression, St Vincent’s Hospital, Sydney

## Duration

1^st^ February, 2010 to 1^st^ August, 2011, inclusive of recruitment, follow up and write up of results. The primary end point will be the end of active treatment for treatment groups 1 and 2 (i.e. 10 weeks after beginning the program) and the secondary time point will be the longer term follow up of these participants (i.e 3 months after completing active treatment).

# Participant section

## Inclusion criteria

Randomised Controlled Trial

The criteria for diagnosis of GAD, social phobia, or panic disorder (with or without agoraphobia) will be based on the Mini International Neuropsychiatric Interview Version 5.0.0 (Appendix A), which is based on DSM-IV diagnostic criteria.

Aged over 18, self identified as suffering from GAD, social phobia or panic disorder (with or without agoraphobia) and have questionnaire scores and results of telephone diagnostic interview consistent with this. Prepared to provide name, phone number and address, and to provide the name and address of a general practitioner and to provide written informed consent. Have access to a phone and computer with a printer.

## Exclusion criteria

Psychosis, bi-polar disorder, substance abuse or dependence disorders, severe depression and or/ current suicidality, or any biological disorder requiring immediate attention.

# Study OUTLINE

## Study Flow Chart

Enrolment (Feb 2010-March 2010)

Randomisation

Pre-treatment “Pre-treatment” assessment

assessment (April) time point (April)

CaCCBT and CCBT Waitlist control

Treatment Phase (10 weeks including “mid treatment

(10 weeks including mid assessment” time point)

treatment assessment)

Post-treatment assessment Pre-treatment assessment (begin

(June) active treatment, June)

Treatment Phase(10 weeks)

3 month follow up (September) Post-treatment assessment (August)

Writeup (2011)

##

## Investigation plan

A CONSORT-R compliant, registered RCT of the intervention (CaCCBT) versus CCBT versus waitlist control group. This will demonstrate whether the benefit from the CaCCBT intervention is superior to natural remission and placebo response. Because of low adherence to CCBT we think that it is a proxy for a placebo treatment. As in any RCT accurate patient selection, good randomization, reliable and valid outcome measures, and low drop-out rates are critical. Analyses based on completers and on intention to treat will be performed.

There are already over 1000 people on the waitlist for Virtual Clinic. In addition, some media attention is expected to generate more publicity to attract people to the program. The study will be described on the intake website, [www.virtualclinic.org.au](http://www.virtualclinic.org.au). People will read the information about the studies and elect to continue or not. If they choose to apply for the study they will complete an automated screening questionnaire. Only people whose responses to the questions meet selection criteria and undergo a brief phone interview explaining the program will read the information sheet and return an electronic consent form and mail that to the investigators. This will trigger the phone interview in which the diagnosis will be confirmed using the Mini International Neuropsychiatric Interview Version 5.0.0 (Appendix A). Questions about the study will be answered and an offer of treatment made.

Patients will be randomly allocated to CaCCBT group (n=50), CCBT group (n=50), or the waitlist group (n=50). Randomization will be done via [www.random.org](http://www.random.org) (see appendix A).

Upon beginning treatment, all participants will complete a set of diagnostic questionnaires. The questionnaires being administered in this study pre and post are the same as the study previously approved by St Vincent's Hospital Human Research Ethics Committee (09/021). However, one additional questionnaire has been added for assessing general anxiety (Depression, Anxiety, Stress Scale, DASS-21, Lovibond & Lovibond, 1995), three questionnaires for diagnosis specific measures of anxiety (Social Interaction Anxiety Scale/Social Phobia Scale Composite Short Form, SPSR, Peters et al, submitted,; Agoraphobic Cognitions Questionnaire, Chambless et al, 1984; Panic Disorder Severity Scale-Self Rating, PDSS-SR, Houck et al, 2002) and one questionnaires for associated variables (NEO-FFI, Costa & McCrae, 1992).

For the treatment groups, [name] and [name] will treat the participants. The treatment program is delivered via the website [www.virtualclinic.org.au](http://www.virtualclinic.org.au). The treatment program consists of 8 lessons conducted over a 10 week period, in which participants are encouraged to complete one lesson per week. The program is comprised of the following Lessons:

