# STUDY OBJECTIVES

## Primary Objectives

The primary objectives of the study is comprised of three hypotheses: 1) That participants in treatment groups 1 and 2 would show significant improvement on a general measure of anxiety (DASS-21) and on disorder specific measures (GAD-7, PSWQ, SPSQ, PDSS-SR) relative to Controls; 2) that participants in treatment groups 1 and 2 with primary diagnoses of GAD, panic, or social phobia would show significant improvement on relevant disorder specific measures (GAD-7, PSWQ, SPSQ, PDSS-SR) relative to controls with the same primary diagnoses; and 3) that treatment groups 1 and 2 will be equivalent regarding generic and diagnosis specific measures of anxiety.

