**Lesson Eight:**

- **Revise the skills you have learnt.**
- **Make a plan for staying well in the future.**

Participants in the CaCCBT group will receive regular email contact with their clinician, and will be encouraged to carry out homework activities.The patients in the CCBT groups will have same access to the lessons, and homework activities as the CaCCBT groups. Unlike the CaCCBT groups, the CCBT groups will have no clinician contact over the 10 week period, but will receive weekly telephone reminders from administrative staff. The waitlist group will not receive any treatment during this period.

After the treatment group has finished the program, all participants will complete a third set of diagnostic questionnaires. The waitlist group, and any CCBT participants wishing to complete the program with clinician contact, will be offered additional treatment after this.

Effectiveness of the CaCCBT program for anxiety will be measured by comparing waitlist and CCCBT and CaCCBT groups on their pre- and post- treatment scores. Long-term follow up data will compare the CaCCBT and CCBT groups at 3 month follow up.

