# STATISTICAL CONSIDERATIONS

## Sample Size Calculation

We would expect pre-post improvement of ES 1.0 for the CaCCBT groups on Anxiety Disorder measures. We also expect the CaCCBT group to improve more than the CCBT group by an ES of 0.3 and waitlist group by an ES of 0.6. Sample size is powered to have an 80% chance of detecting differences at p<.05.

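### Section 5.2 says the trial will show whether CaCCBT beats placebo response, but CCBT is an active arm by the protocol's own account and no contrast isolates placebo response

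*Protocol*

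**What the plan says.** Section 5.2 of the protocol (Investigation plan) introduces the three-arm design and then states what it will show: "This will demonstrate whether the benefit from the CaCCBT intervention is superior to natural remission and placebo response". The only support given for the placebo part is the next sentence: "Because of low adherence to CCBT we think that it is a proxy for a placebo treatment". No adherence figure for CCBT is given.

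The same section, after the lesson list, describes the arms. On CCBT: "The patients in the CCBT groups will have same access to the lessons, and homework activities as the CaCCBT groups". These participants have no clinician contact but "will receive weekly telephone reminders from administrative staff". On the third arm: "The waitlist group will not receive any treatment during this period".

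Section 2.1 (Primary Objectives) counts CCBT as treatment group 2. Hypothesis 1 is that "participants in treatment groups 1 and 2 would show significant improvement on a general measure of anxiety (DASS-21") and on the disorder-specific measures, relative to controls. Hypothesis 3 is "that treatment groups 1 and 2 will be equivalent regarding generic and diagnosis specific measures of anxiety".

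Section 8.1 (Sample Size Calculation) expects "the CaCCBT group to improve more than the CCBT group by an ES of 0.3 and waitlist group by an ES of 0.6". Section 7 says that there is no blinding.

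**The concern.** A placebo comparison needs an arm that carries the nonspecific elements (expectancy, attention, being in a programme) without the active content. CCBT carries the active content. Subtracting it from CaCCBT removes the shared CBT programme, which is the very ingredient whose specific effect a placebo comparison should isolate. The waitlist has the opposite fault: it lacks the active content and the nonspecific elements alike.

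What is at stake is the conclusion drawn from the results. A CaCCBT–CCBT difference could be reported as efficacy over placebo when it shows the value of clinician contact. A null difference could be reported as no better than placebo when the shared programme works in both arms. A CCBT–waitlist difference would be a treatment success under Hypothesis 1 and a placebo response under section 5.2.

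**Working it through.** **1. The passages side by side**

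| Place in the protocol | What CCBT is |
|---|---|
| 5.2, rationale | Proxy for placebo, because of low adherence |
| 5.2, arm description | Same lessons and homework as CaCCBT, with weekly reminder calls |
| 2.1, Hypothesis 1 | A treatment expected to beat controls |
| 2.1, Hypothesis 3 | Expected to be equivalent to CaCCBT |
| 1.1, aim | One level of support, in a study of how much support people need |

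The first row is the outlier. Low adherence would make CCBT a partial dose of the active programme, not an inert control, and the reminder calls support adherence. If the first and fourth rows were both right, confirming Hypothesis 3 would mean that CaCCBT equals placebo, so a primary hypothesis would succeed by defeating the claim in section 5.2.

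**2. Inputs for an illustration**

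- From the protocol: 50 per arm (3.3); standardised effects of CaCCBT of 0.3 over CCBT and 0.6 over waitlist, and 80% power at p<.05 (8.1).
- By subtraction: CCBT over waitlist = 0.6 − 0.3 = 0.3.
- Assumed: two-sided test (sidedness is not stated), SD 1, no baseline adjustment, and the placebo response over waitlist, called p, which the documents do not give.

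**3. The plan's own figure**

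n per arm = 2(1.960 + 0.842)²/d². For d = 0.6 this gives 44; for d = 0.3 it gives 175.

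Power at 50 per arm = Φ(d/√(2/50) − 1.960), with √(2/50) = 0.2:

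- d = 0.6: Φ(3.0 − 1.96) = 85%
- d = 0.3: Φ(1.5 − 1.96) = 32%

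So 50 per arm meets the 80% target for the waitlist contrast but not for the CCBT contrast. That shortfall is a separate matter; more patients would not turn CCBT into a placebo.

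**4. A true advantage over placebo that is missed**

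The true CaCCBT–placebo effect is 0.6 − p. The CCBT contrast sees 0.3 whatever p is.

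| Assumed p | True effect over placebo | Power, true placebo arm | Power, CCBT contrast | Loss (points) |
|---|---|---|---|---|
| 0 | 0.6 | 85% | 32% | 53 |
| 0.1 | 0.5 | 71% | 32% | 38 |
| 0.2 | 0.4 | 52% | 32% | 19 |
| 0.3 | 0.3 | 32% | 32% | 0 |

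Losses are taken from unrounded powers (for example 70.5 − 32.3 = 38.2). The last row is the one case in which the proxy is exact: the whole expected CCBT–waitlist difference of 0.3 would have to be placebo response.

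Baseline adjustment multiplies the SD by √(1 − r²). With an assumed pre-post correlation of 0.5 or 0.7, the first row becomes 93% against 41%, or 99% against 56%. The gap remains.

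**5. An absent advantage over placebo that is declared**

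Suppose that CaCCBT's benefit over waitlist is wholly nonspecific, of size g. The waitlist contrast is then significant with probability Φ(g/0.2 − 1.96) + Φ(−g/0.2 − 1.96):

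| Assumed g | 0.2 | 0.3 | 0.5 | 0.6 |
|---|---|---|---|---|
| Significant | 17% | 32% | 71% | 85% |

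The test is working correctly here, since there is a real difference from no treatment. The error arises only if that result is read as superiority to placebo.

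**The case against.** The strongest reply is that no placebo test is planned. Placebo appears only in two sentences of section 5.2, one of them put as the authors' opinion. The objectives, hypotheses, sample size and analysis plan never mention it. This stands, and it limits the point. A reader might infer that the protocol sets up a formal null hypothesis against placebo whose error rates are wrong. It does not, so the percentages above describe how far a conclusion could mislead; they are not error rates of a planned analysis. But section 5.2 still says what the trial will demonstrate, and stating the proxy assumption openly does not make it agree with the arm description or the hypotheses.

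A reader might also infer a loss of over 80 points, by supposing 0.6 over placebo in both internet arms and nothing added by the clinician (85% against 2.5% in favour of CaCCBT). That combines zero placebo response with zero clinician effect, and the second conflicts with the 0.3 expected in section 8.1. The documents do not support it as the headline figure.

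Nor do they support calling the CCBT contrast's 32% a false-positive rate. That would require counting clinician contact as placebo, whereas in this protocol clinician contact is part of what defines CaCCBT. The reminder calls also give CCBT some contact, so attention is partly controlled in that contrast.

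Finally, the natural-remission half of the sentence is sound: the waitlist is a suitable comparator for it.

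**Conclusion.** The point holds for the placebo half of the sentence. CCBT is described and hypothesised as an active treatment, the waitlist is untreated and unblinded, and so no contrast among the three arms isolates placebo response. A statistical analysis plan could not repair this, because it follows from the arms.

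The size depends on a placebo response that the documents do not give. Under the assumptions above and without baseline adjustment, the loss of power against a true placebo arm runs from 0 to about 53 points for placebo responses of 0 to 0.3. A wholly nonspecific benefit would make the waitlist contrast significant about 17% to 85% of the time for effects of 0.2 to 0.6. The contradiction itself needs none of these assumptions.

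It would be too much to infer that the randomised comparisons are invalid. Each remains valid for what it estimates; what is wrong is the label that section 5.2 puts on them.

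**What to change.** In section 5.2, end the claim at natural remission by deleting the reference to placebo response, and delete the sentence that makes CCBT a placebo proxy. In their place, state that:

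- CaCCBT versus waitlist and CCBT versus waitlist each estimate the effect of the programme package, nonspecific effects included, over the natural course;
- CaCCBT versus CCBT estimates the added effect of clinician contact over administrative reminders;
- the trial supports no conclusion about superiority to placebo.

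This brings section 5.2 into line with the support question in section 1.1, the hypotheses in section 2.1 and its own description of the arms. It is a wording amendment and needs no new patients, data or analyses. The cost is giving up the placebo claim. It does not settle the separate tension between the equivalence in Hypothesis 3 and the 0.3 difference expected in section 8.1.

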**Lesson One:**

- **Learn about the physical, cognitive and behavioural symptoms of anxiety.**
- **Learn about treatments for anxiety**

**Lesson Two:**

- **Learn about the relationship between the way you think and feel.**
- **Begin monitoring and challenging unhelpful thinking patterns.**

**Lesson Three:**

- **Learn about your body and anxiety**
- **Controlling physical symptoms and maintaining physical balance**

**Lesson Four:**

- **Learn about behaviours that make anxiety worse**
- **Design a plan for confronting problems, slowly and gradually.**

**Lesson Five:**

- **Learn more about challenging unhelpful thinking patterns, and how to change the way you think**
- **Learn about structured problem solving**

**Lesson Six:**

- **Learn more about behaviours that make anxiety worse, and how troubleshooting common barriers to improvement**
- **Learn about how to put the skills together**

**Lesson Seven:**

- **Learn additional skills for tackling anxiety**
- **Learn about assertiveness and effective communication.**
- **Learn about the role of self-criticism in anxiety.**

**Lesson Eight:**

- **Revise the skills you have learnt.**
- **Make a plan for staying well in the future.**

Participants in the CaCCBT group will receive regular email contact with their clinician, and will be encouraged to carry out homework activities.The patients in the CCBT groups will have same access to the lessons, and homework activities as the CaCCBT groups. Unlike the CaCCBT groups, the CCBT groups will have no clinician contact over the 10 week period, but will receive weekly telephone reminders from administrative staff. The waitlist group will not receive any treatment during this period.

After the treatment group has finished the program, all participants will complete a third set of diagnostic questionnaires. The waitlist group, and any CCBT participants wishing to complete the program with clinician contact, will be offered additional treatment after this.

Effectiveness of the CaCCBT program for anxiety will be measured by comparing waitlist and CCCBT and CaCCBT groups on their pre- and post- treatment scores. Long-term follow up data will compare the CaCCBT and CCBT groups at 3 month follow up.

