## Study Procedure risks

In applying to join the program, patients with severe depression/suicidality will be screened out and encouraged to see their GP. Patients will need to meet inclusion/exclusion criteria before joining the study. After satisfying these criteria, patients will be measured at pre-treatment, mid-treatment, post-treatment time points, with CaCCBT and CCBT groups measured at 3 month follow up and the waitlist control group measured immediately after completing the active treatment phase. If any responses to questionnaires at any of these timepoints indicate deterioration in wellbeing, this will be raised with the Chief Investigator, and or clinician to determine the best way of dealing with these difficulties. Additionally, regular team meetings (at least 3 times a week) will be conducted to monitor any difficulties patients may be having and ways of best dealing with these difficulties. Adverse events will be monitored by the investigators and reported to the Ethics Committees.

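### The 3-month CaCCBT–CCBT comparison does not isolate clinician support, because CCBT participants may take the clinician-assisted programme before that follow-up

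*Protocol*

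**What the plan says.** Section 5.2 (closing paragraphs, after the lesson list) separates the two active arms by clinician contact: CaCCBT participants have regular e-mail contact with a clinician, while CCBT participants have none during the 10 weeks and receive reminder calls from administrative staff. When treatment ends, "all participants will complete a third set of diagnostic questionnaires". Section 5.3 gives the order of assessments: "patients will be measured at pre-treatment, mid-treatment, post-treatment time points". The third set is therefore the post-treatment one.

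Section 5.2 then says, in the same sentence that offers treatment to the waitlist group, that "any CCBT participants wishing to complete the program with clinician contact, will be offered additional treatment after this". The paragraph after it says: "Long-term follow up data will compare the CaCCBT and CCBT groups at 3 month follow up". Section 3.5 makes the end of active treatment the primary end point, and "the secondary time point will be the longer term follow up of these participants".

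The flow chart in 5.1 places post-treatment in June. Its last assessments for the two columns read "3 month follow up (September) Post-treatment assessment (August"): September for the active arms, August for the waitlist group after its own 10-week course. It shows no further treatment for CCBT.

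Hypothesis 3 in section 2.1 is "that treatment groups 1 and 2 will be equivalent regarding generic and diagnosis specific measures of anxiety". Section 8.1, by contrast, says the investigators "expect the CaCCBT group to improve more than the CCBT group by an ES of 0.3". Sections 5.2 and 8.2 promise completer and intention-to-treat analyses.

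**The concern.** The two active arms differ by design in one thing, clinician contact. The protocol lets any CCBT participant obtain that contact once the post-treatment questionnaires are done, then compares the arms by their original names three months later. If a material share accept, the follow-up no longer shows what clinician support adds, although section 1.1 names the level of support needed as a question of interest.

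Acceptance is voluntary and plausibly more common among people who are still unwell. Leaving them out, or analysing completers only, would therefore compare selected groups. What is at stake is the meaning of the secondary time point, and any statement about lasting equivalence or lasting advantage drawn from it.

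**Working it through.** **1. Does a second course fit before follow-up?** Post-treatment is in June and follow-up in September, about 13 weeks apart. The programme lasts 10 weeks (5.2). The waitlist group's own course, begun in June, ends in August on the flow chart. A CCBT participant who starts alongside the waitlist group can finish before follow-up.

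**2. The protocol's own figure for this contrast.** Section 8.1 expects a difference of 0.3 and states 80% power at p<.05, with 50 per arm (3.3). With SD 1, SE = √(2/50) = 0.2, and two-sided power = Φ(d/SE − 1.96) + Φ(−d/SE − 1.96). At d = 0.3 this is Φ(−0.46) + Φ(−3.46) = 0.32, so 80% does not reproduce. Baseline adjustment with an assumed correlation of 0.3 to 0.7 gives 35% to 56%. That is a separate matter, and the present point does not depend on it.

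**3. Size of the dilution.** Let c be the share of CCBT participants who accept and g their mean extra gain in SD units by 3 months. Neither is in the documents, so both are assumed over a range. Also assumed is that the 0.3 would have lasted to 3 months had no one accepted. Then

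3-month difference = 0.3 − c × g.

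| Take-up c | g = 0.15 | g = 0.3 (full catch-up) | g = 0.6 |
|---|---|---|---|
| 0% | 0.30 | 0.30 | 0.30 |
| 25% | 0.263 | 0.225 | 0.15 |
| 50% | 0.225 | 0.15 | 0 |
| 75% | 0.188 | 0.075 | −0.15 |
| 100% | 0.15 | 0 | −0.30 |

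**4. Direction if the arms are truly equal.** With a true difference of 0, the formula becomes −c × g. At c = 50% and g = 0.3 the difference is −0.15: CCBT moves ahead, away from equivalence.

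**5. Effect on a superiority test.** With g = 0.3 and 50 per arm, the formula in step 2 gives power of 32%, 20%, 12% and 7% at 0%, 25%, 50% and 75% take-up. The chance of a non-significant result is 68%, 80%, 88% and 93%.

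**6. Effect on an equivalence test.** No margin is stated in the protocol. With an assumed margin of 0.5 SD and two one-sided 5% tests, the limits for the estimate are ±(0.5 − 1.645 × 0.2) = ±0.171. The chance of declaring equivalence is about 25%, 37%, 49% and 58% at true differences of 0.30, 0.225, 0.15 and 0.075. With a margin of 0.3, 1.645 × 0.2 = 0.329 exceeds the margin, so equivalence is practically out of reach at any take-up.

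**The case against.** The strongest reply has four parts.

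- **A valid estimand remains.** An intention-to-treat comparison at 3 months still correctly describes CCBT followed by optional clinician contact. This stands, and it is why the comparison should be kept and relabelled. It does not make the comparison one of programme against programme.
- **Timing is inferred.** Section 5.2 says only that the offer comes after the questionnaires, and the flow chart shows a second course for the waitlist group alone. True, but the CCBT offer shares a sentence with the waitlist offer, and nothing holds it back until September. That the flow chart does not show it is itself something to reconcile.
- **An analysis plan could deal with it.** The handling of later scores may indeed be left to one. But the protocol itself fixes both the offer and the comparison, and neither promised analysis set resolves the conflict. A start date that is not recorded at the time may not be recoverable.
- **Only a secondary comparison is touched.** This stands. The primary assessment precedes the offer.

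A reader might also infer that the offer must push the result towards equivalence, that it favours Hypothesis 3, or that a null result at 3 months is almost assured. The documents do not support these readings. The direction depends on CaCCBT being better and on those who accept gaining no more than the gap (steps 3 and 4). Section 2.1 ties Hypothesis 3 to no time point, and a non-significant difference would not establish equivalence anyway. The chance of a null result is 80% at 25% take-up, and 68% of that is present with no take-up at all because of the sample size.

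**Conclusion.** The point holds for the 3-month comparison only. As the protocol stands, that comparison measures CaCCBT against CCBT with optional clinician-assisted treatment, and cannot be read as the value of clinician support or as equivalence of the two programmes. Its size cannot be fixed from the documents. On the expected difference of 0.3 with full catch-up, each 10% of take-up removes 0.1 × 0.3 = 0.03 SD, so half the difference is gone at 50% take-up. With a gain of 0.6 it is gone entirely at 50% and reversed at 100%. Take-up, gain and persistence of the 0.3 are all assumptions. The conclusion about what is being estimated needs none of them, only that some CCBT participants accept before follow-up. It should be put right, but it does not threaten the primary result.

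**What to change.** Leave the offer of care as it is and change the record, the labelling and the claim.

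1. Reconcile the flow chart in 5.1 with the text of 5.2 on whether and when CCBT participants may have clinician contact before the 3-month assessment.
2. Record the start date of any such contact for each CCBT participant, and report take-up.
3. Keep the as-randomised 3-month comparison, labelled as CaCCBT versus CCBT with optional clinician contact.
4. State that any conclusion on Hypothesis 3 rests on the post-treatment assessment, not on the 3-month data.
5. Add, as a sensitivity analysis, a mixed model on all randomised participants in which CCBT scores after clinician contact begins are treated as missing given that person's earlier scores. State the missing-at-random assumption, which requires the earlier scores to capture why people accepted.

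The cost is one recorded date, some wording and one extra analysis. The sensitivity analysis can lose much precision, since each person who accepts has only one later score: at 75% take-up about 50 × 0.25 = 12.5, or roughly 12 of 50 CCBT participants, would contribute a 3-month score, before any drop-out. For that reason it should not be the main analysis.
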